## Abstract

**Background:**

Survival is poorer in elderly patients with head and neck squamous cell carcinomas [HNSCCs] than in younger patients. Possible explanations include a contribution of co-morbidities to mortality, frequent refusal of standard therapy, and the use of suboptimal treatments due to concern about toxicities. The Comprehensive Geriatric Assessment [CGA] is a multidimensional assessment of general health that can help to customise treatment and follow-up plans. The CGA has been proven effective in several health settings but has not been evaluated in randomised studies of patients with cancer. Our aim here was to assess the impact of the CGA on overall survival, function, and nutritional status of elderly patients with HNSCC.

**Methods/design:**

EGeSOR is an open-label, multicentre, randomised, controlled, parallel-group trial in patients aged 70 years or older and receiving standard care for HNSCC. The intervention includes four components: the CGA conducted by a geriatrician before cancer treatment, participation of the same geriatrician in cancer treatment selection, a standardised geriatric therapeutic intervention designed by the same geriatrician; and geriatric follow-up for 24 months. The primary endpoint, assessed after 6 months, is a composite criterion including death, functional impairment [Activities of Daily Living score decrease ≥2], and weight loss ≥10%. Secondary endpoints include progression-free survival, unscheduled admissions, quality of life, treatment toxicities, costs, and completion of the planned cancer treatment. A centralised online system is used to perform 1:1 randomisation with a minimisation algorithm for centre, age, T and N stages, and tumour site [oral, oropharyngeal, hypopharyngeal, or laryngeal]. The estimated sample size is 704 patients, who are being recruited by 14 centres in 9 French cities.

**Discussion:**

EGeSOR is the first randomised trial of the CGA in elderly cancer patients. We expect the CGA to have direct clinical benefits on the management of elderly patients with HNSCC. If this expectation is fulfilled, the trial may lead to modifications of the management model for elderly patients with cancer.

**Trial registration:**

Trial registration:
NCT02025062

## Background

Head and neck cancers are the sixth most common cancer in the world according to 2006 European Cancer Observatory data
[1]. In parallel with the rise in life expectancy, the number of elderly patients with head and neck squamous cell carcinomas [HNSCCs] is increasing, especially in women
[2,3]. Overall survival [OS] in patients with HNSCCs has been estimated at about 50% after 5 years, with large variations across tumour sites
[4-6]. Two studies suggest lower 5-year OS rates in patients aged 75 or over than in younger patients
[7,8]. Possible explanations to this difference may include a contribution of co-morbidities to mortality
[7,9], greater patient reluctance to undergo full treatment regimens, and physician choice of suboptimal treatments due to concern about toxicities
[10]. Co-morbidities become increasingly prevalent with advancing age and are associated with treatment-related side effects and poorer outcomes
[9,11-13]. Although studies support the use of similar cancer treatments in older and younger patients
[14,15], a thorough pre-treatment evaluation is deemed crucial, most notably in elderly patients
[16-18].

The Comprehensive Geriatric Assessment [CGA] was developed by geriatricians as a ‘multidimensional interdisciplinary diagnostic process focussed on determining a frail older person’s medical, psychological, and functional ability in order to develop a coordinated and integrated plan for treatment and long-term follow-up’
[19]. The CGA relies on validated geriatric scales or tests to draw a detailed picture of the patient’s health status, which can then serve to develop an individualised geriatric intervention plan. The CGA is therefore both a diagnostic and a therapeutic tool. It is designed to ensure that all problems are identified, quantified, and managed appropriately. A meta-analysis showed that the CGA, combined with multidisciplinary interventions, improved survival and function and decreased the need for admission and institutionalisation in elderly patients with non-malignant diseases
[20]. Over the past decade, the CGA has been suggested for elderly patients with cancer and recommended by the International Geriatric Oncology Society [SIOG]
[21] as a means of optimising cancer treatment selection, improving the chances of treatment completion, increasing survival, and diminishing adverse outcomes
[22-24]. However, randomised trials of the CGA are available only for non-malignant conditions: there is no high-level evidence on the potential benefits of the CGA in elderly patients with cancer.

We hypothesised that performing the CGA in elderly patients with HNSCC would improve treatment decision-making by better evaluating the patient’s functional reserve, a crucial factor in the ability to tolerate cancer treatments; and would improve OS, function, and nutritional status by ensuring optimal customisation of the treatments and follow-up during surgery and/or radiotherapy and/or chemotherapy. Our objective was to evaluate the impact of the CGA on OS, function, and nutritional status of elderly patients with HNSCC.

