## Methods/design

### Study design and setting

We are conducting an open-label, multicentre, parallel-group, randomised, controlled trial in patients aged 70 years or older and receiving standard care for HNSCC. One group receives a CGA-based multi-component intervention and the other does not [Figure 
1]. The primary endpoint is a composite criterion to be assessed after 6 months. Other endpoints such as OS and disease-free survival are assessed after 24 months. The patients are being recruited at 14 ENT/maxillo-facial surgery departments in 13 hospitals located in 9 cities in France [Paris, Créteil, Montfermeil, Villeneuve-Saint-Georges, Lille, Strasbourg, Nancy, Nantes, and Suresnes]. The protocol was approved by the appropriate ethics committee [CPP Ile-de-France I, Paris, France, approval April, the 20 April 2013;13213]. The trial is registered on ClinicalTrials.gov [NCT02025062].

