#### (a) CGA

The CGA is performed by the intervention geriatrician, after randomisation and before the multidisciplinary meeting during which the cancer-treatment plan is established. The CGA consists in a detailed medical, psychological, and social assessment including a careful medical history and physical examination. In accordance with SIOG recommendations for elderly cancer patients, seven domains are assessed routinely: functional status, mobility and fall risk, nutritional status
[25], cognitive status, mood, co-morbidities and medications, and social environment. These domains are assessed using validated tests, questionnaires, scores, and/or scales [Table 
1]. Pain is also evaluated using a verbal numeric scale. The CGA is performed by a senior geriatrician, in some cases with help from a trained healthcare worker [usually a nurse working in the oncology and/or geriatric department].

**Table 1 T1:** Primary and secondary endpoints in the EGeSOR trial

**Endpoints**	**Time assessed**	**Description**
Primary endpoint	6 months after randomisation	Composite criterion including
		- death,
		- at least 2-point decrease in the Activities of Daily Living (ADL) score versus baseline
		- at least 10% decrease in body weight versus baseline
Secondary endpoints	6, 12, and 24 months after randomisation	- each component of the primary endpoint
		- progression-free survival
		- in-hospital death
		- unplanned admissions
		- post-surgery hospital stay length
		- discharge to home or nursing home
		- final cancer treatment plan (surgery, chemotherapy, targeted therapies, radiotherapy, and/or supportive care, alone or combined)
		- quality of life assessed by EORTC QLQ-C30 and specific module for head and neck cancer H&N35
		- treatment toxicities and/or complications: chemotherapy toxicities according to Classification Common Terminology Criteria for Adverse Events (CTCAE version 4.02)
		- cancer treatment feasibility
		- costs

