#### (b) Geriatrician participation in development of the cancer-treatment plan

The intervention geriatrician lists all identified problems by order of priority and provides specific advice on the treatment goal [curative or palliative] and modalities [surgery, radiotherapy, chemotherapy, targeted therapy, and supportive care, used sequentially or simultaneously] in a written report given to the ENT physicians in charge of cancer treatment. The intervention geriatrician then participates in the multidisciplinary meeting held to determine the cancer-treatment plan
[23].

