#### (d) Geriatric follow-up

The standardised geriatric follow-up provided by the intervention geriatrician, consists in a brief assessment of nutrition, mood, pain, functional status, the five above-listed co-morbidities, self-perceived health status, medication use, and implementation of the multidimensional geriatric therapeutic programme. The results of this standardised follow-up are used to make recommendations to the ENT physician, oncologist, radiotherapist and general practitioner.Follow-up includes closely spaced physical examinations for 1 to 6 months depending on the treatment modalities; Figure 
2 is an example for a surgically managed patient. After completion of the initial cancer treatment, the intervention geriatrician or nurse phones the patient every 3 months during the first 2 years after randomisation. If problems are identified during any of these phone calls, an appointment for a visit with the intervention geriatrician is scheduled.

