### Endpoints

Table 
2 shows the primary and secondary endpoints. The primary endpoint is a composite criterion evaluated 6 months after randomisation and including death, an at least 2-point decrease in the Activities of Daily Living [ADL] score
[27] versus baseline, and at least 10% weight loss versus baseline. A clinical research assistant blinded to the randomisation arm uses a standardised measurement guide to adjudicate the ADL score and weight. Weight is measured to the nearest 0.1 Kg using an electronic scale [Seca Model 876, Birmingham, United Kingdom]. Our decision to include functional and nutritional measures into the primary endpoint rests both on sound evidence that these measures influence treatment feasibility, patient survival, and quality of life; and on the potential for appropriate management to reverse functional impairments and weight loss.

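### Overall survival is a stated objective and a 24-month endpoint, but Table 1 and the abstract do not name it, the default analysis treats it as a proportion, and a positive 6-month composite carries no limit on what may be claimed

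*Protocol article*

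**What the plan says.** All references are to the protocol article.

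- **Objective (Background; the abstract agrees).** "Our objective was to evaluate the impact of the CGA on OS, function, and nutritional status of elderly patients with HNSCC". There are three outcomes, with OS named first.
- **Study design and setting.** "Other endpoints such as OS and disease-free survival are assessed after 24 months".
- **Endpoints.** "The primary endpoint is a composite criterion evaluated 6 months after randomisation and including death"; the other two components are an ADL loss of at least 2 points and a weight loss of at least 10%, both against baseline.
- **Table 1.** The secondary endpoints, at 6, 12 and 24 months, include "each component of the primary endpoint", progression-free survival and in-hospital death. OS does not appear under that name, nor does disease-free survival. The abstract's list of secondary endpoints also has progression-free survival and no OS.
- **Statistical analysis.** The primary is compared by Pearson's chi-square test with a relative risk and an absolute difference. Secondary endpoints follow the same method. The only departure stated there is mixed models for serially measured variables.
- **Intervention, component (b).** The geriatrician "provides specific advice on the treatment goal [curative or palliative] and modalities", then takes part in the meeting that settles the plan.
- **Discussion and Conclusion.** The trial aims to show a gain on the 6-month composite. If benefit is shown, the care model for elderly cancer patients may change. No statement links either conclusion to 24-month survival.

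**The concern.** There are three linked weaknesses.

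First, the survival endpoints are not stated consistently. The objective and the design section promise OS, while the two places where a reader looks up the endpoints do not name it. The second survival endpoint has two different names, which usually stand for different event definitions.

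Second, the stated default for secondary endpoints is a comparison of proportions. Applied to survival over 24 months, it treats a death in month 7 like a death in month 23, and it has no proper place for a patient whose follow-up ends before 24 months.

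Third, the one powered test is read at 6 months and gives a weight loss of 10% the same weight as a death. It cannot see deaths after month 6, and a small excess before month 6 can be outweighed by fewer non-fatal events. Survival matters here because the intervention includes advice on treatment goal and modality, and because the Background lists "physician choice of suboptimal treatments due to concern about toxicities" among the possible reasons for poorer survival in the elderly. At stake is whether a positive 6-month result would be read as answering the survival part of the objective.

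**Working it through.** **1. Reproduce the plan's own figure.** Inputs from Sample size estimation: 30% versus 20%, two-sided 5%, 80% power, 320 per group, then 704 in all for 10% losses.

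- Two-proportion formula: n = [1.96·√(2·0.25·0.75) + 0.842·√(0.21 + 0.16)]² / 0.10² = 294 per group, 588 in all.
- With continuity correction: 313 per group, 626 in all, within 3% of the stated 640.
- Power at 320 per group: 83% uncorrected, 81% with the correction.
- 640 × 1.10 = 704.

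No stated figure is wrong. The size is set for the composite alone.

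**2. Can the composite improve while early deaths rise?** The protocol does not split the 30% into deaths and non-fatal events, so these splits are assumptions. With d the proportion dead at 6 months and f the proportion of survivors with an ADL or weight event, composite = d + (1 − d)·f.

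- Control: 0.10 + 0.90 × 0.22 = 0.298.
- Intervention: 0.12 + 0.88 × 0.10 = 0.208.

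Evaluable patients: 704 × 0.90 = 633.6, about 317 per arm.

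- Composite: the mean proportion is 0.253, the pooled standard error √(2·0.253·0.747/317) = 0.03453 and the unpooled one 0.03435. Power = Φ[(0.090 − 1.96 × 0.03453)/0.03435] = Φ(0.65) = 74%.
- Deaths, 10% versus 12%, same formula: both standard errors are about 0.0248–0.0249, giving Φ(−1.16) = 12%.

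If instead the composite is held at 30% versus 20% with 320 per group, and control deaths are set at 5%, 10% or 15%, a 2-point excess of deaths would be detected with power of 18%, 13% and 10%.

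**3. What can the 24-month data show?** The protocol gives no 24-month death rate, so the counts are assumptions. With D deaths and equal arms, the 95% CI for the hazard ratio is the estimate multiplied and divided by exp(1.96 × 2/√D).

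| Deaths D | CI factor |
|---|---|
| 200 | 1.32 |
| 280 | 1.26 |
| 350 | 1.23 |

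With assumed control deaths of 30%, 40% or 50% by 24 months and 320 per group, a 5-point excess has log-rank power of 25% to 28% and chi-square power of 24% to 27%. A 10-point excess has 74% to 77% and 72% to 76%. Under these assumptions the time-to-event analysis gains little power. Its value lies in using the timing of deaths and handling censoring. The OS estimate is informative, but a non-significant OS test would not rule out a moderate harm.

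**4. The passages side by side.**

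| Item | Design section | Table 1 | Statistical analysis |
|---|---|---|---|
| OS | named, 24 months | death as a component, 6, 12 and 24 months | chi-square, relative risk by default |
| Second survival endpoint | disease-free survival | progression-free survival | same default |

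**The case against.** The case on the other side is strong on several points, and much of it stands.

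- The objective has three parts, and the composite matches them one by one: death, function, weight. A reader might infer that OS is the sole aim and that the trial measures something else; the text does not support that.
- Survival is not absent. Death is a separate secondary endpoint in Table 1 at 24 months. What is missing is the name and a time-to-event definition.
- A reader might infer that lighter treatment could count as success whatever it does to survival. That goes too far. Every death by month 6 counts against the intervention.
- A reader might infer that month 6 falls just as the longest treatments end. The only hint is "Follow-up includes closely spaced physical examinations for 1 to 6 months depending on the treatment modalities", which describes geriatric examinations. No section says when treatments end or when weight and functional loss peak.
- A shift towards lighter treatment is also an inference. The geriatrician advises a multidisciplinary meeting, all patients are to receive standard therapy, and the Background cites the CGA as a means of improving treatment completion and survival. Table 1 already records the final treatment plan and treatment feasibility.
- The composite is disclosed as a limitation and justified in the Discussion: a single endpoint would have needed too many patients.
- Hazard ratios and interpretation rules are often left to an analysis plan, which is not shown here.

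The last point answers only part of the concern. The article does not leave the method for secondary endpoints open; it sets one that suits survival poorly. The feasibility argument supports a composite primary, but not an unnamed OS endpoint or two names for the other survival endpoint.

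**Conclusion.** The point holds as a fault of endpoint definition, analysis method and scope of claim. It is not an error in the choice of primary endpoint or in the sample size. Three things rest on the text alone: OS is promised but not named in the endpoint lists, progression-free and disease-free survival are used for the same place, and survival falls under a comparison of proportions.

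The fourth, that a positive composite can sit beside slightly more early deaths or worse survival after month 6, is a property of the endpoint. Its size here (deaths 10% versus 12%, composite 29.8% versus 20.8%, 74% power for the composite and 12% for the deaths) is an illustration under assumed splits. It shows what is possible, not what is likely.

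A reader might also conclude that the trial cannot address its survival objective. It can: under an assumed 200 to 350 deaths, the planned 24-month follow-up would give a hazard ratio with a CI factor of 1.32 to 1.23. The plan should be corrected on these points, but the design can stand.

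**What to change.** 1. Name OS in Table 1 and in the abstract as the first secondary endpoint, defined as time from randomisation to death from any cause, to 24 months.
2. Analyse OS as time to event, with a hazard ratio and 95% CI, in place of the chi-square default in Statistical analysis.
3. Choose one term, progression-free or disease-free survival, define its events, use it throughout, and analyse it in the same way.
4. State that a positive 6-month result supports a claim on the composite only, reported with its split into deaths, ADL loss and weight loss. State that any survival claim rests on the 24-month OS estimate and its interval.

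The cost is wording in the abstract, Table 1, Statistical analysis and Conclusion. No extra patients are needed, and the 24-month assessment is already planned; exact dates of death and of last contact must be available. The downside is that the 6-month result carries a narrower claim until the 24-month data are in.

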## Methods/design

### Study design and setting

We are conducting an open-label, multicentre, parallel-group, randomised, controlled trial in patients aged 70 years or older and receiving standard care for HNSCC. One group receives a CGA-based multi-component intervention and the other does not [Figure 
1]. The primary endpoint is a composite criterion to be assessed after 6 months. Other endpoints such as OS and disease-free survival are assessed after 24 months. The patients are being recruited at 14 ENT/maxillo-facial surgery departments in 13 hospitals located in 9 cities in France [Paris, Créteil, Montfermeil, Villeneuve-Saint-Georges, Lille, Strasbourg, Nancy, Nantes, and Suresnes]. The protocol was approved by the appropriate ethics committee [CPP Ile-de-France I, Paris, France, approval April, the 20 April 2013;13213]. The trial is registered on ClinicalTrials.gov [NCT02025062].

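### The disease-control secondary endpoint has two names: disease-free survival in the design section, progression-free survival in the abstract and Table 1

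*Protocol article*

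**What the plan says.** Three places in the protocol article name the outcome.

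- **Study design and setting:** "Other endpoints such as OS and disease-free survival are assessed after 24 months".
- **Abstract, Methods/design:** "Secondary endpoints include progression-free survival, unscheduled admissions, quality of life, treatment toxicities, costs, and completion of the planned cancer treatment".
- **Table 1 (printed under the CGA heading):** "progression-free survival" is a secondary endpoint, assessed "6, 12, and 24 months after randomisation". DFS is not listed.

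The article defines neither term.

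Three further statements bear on whether the names can be exchanged.

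- The CGA takes place "after randomisation and before the multidisciplinary meeting during which the cancer-treatment plan is established".
- In the intervention arm the geriatrician "provides specific advice on the treatment goal [curative or palliative] and modalities".
- Table 1 makes the treatment plan itself an outcome: "final cancer treatment plan (surgery, chemotherapy, targeted therapies, radiotherapy, and/or supportive care, alone or combined".

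The Statistical analysis section sets intent-to-treat for the primary endpoint, with a Pearson chi-square test, a relative risk and an absolute difference. It carries that method over to the between-group comparisons of secondary endpoints. Mixed models are reserved for serially measured variables, and PFS and OS are not among those.

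**The concern.** DFS and PFS both describe disease control, but they need different things of the patient. On its usual meaning, DFS starts from a disease-free state. PFS needs only a starting date and follow-up for progression or death.

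In a trial confined to curative resection the difference could be small. Here, Study population admits patients aged 70 or over at macroscopic diagnosis with no requirement of curative intent, and supportive care is a possible final plan. Some patients may therefore never have a DFS time in the ordinary sense.

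Two things are at stake. First, a reader of this open-label trial cannot tell from the article which outcome will be reported at 24 months. Second, if DFS were adopted and limited to patients made disease-free, the groups compared would no longer be the groups randomised.

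**Working it through.** **1. The names side by side.**

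| Place | Term | Time |
|---|---|---|
| Abstract | PFS | not given |
| Study design and setting | DFS (as an example, with OS) | 24 months |
| Table 1 | PFS | 6, 12 and 24 months |

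DFS occurs once in the article and is missing from the table that lists the endpoints. Either it is a slip for PFS or it is an additional, unlisted endpoint. Both need correcting.

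**2. Does the label matter here?** Randomisation comes first, then the CGA, then the advice on treatment goal, then the treatment plan. The advice is part of the intervention, so the proportion and type of patients made disease-free can differ between arms. PFS from randomisation does not depend on that status.

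**3. Direction of bias if DFS were limited to patients made disease-free.** The documents give no figures for this, so every input below is an assumption.

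- 60% of patients are fit and 40% frail.
- 24-month DFS is 65% in fit and 35% in frail patients, with no true effect of the intervention.
- 90% of fit patients in each arm enter the disease-free subset.
- A share s of frail patients enters it, with s = 0.60 in controls.

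Subset DFS = (0.6 × 0.9 × 0.65 + 0.4 × s × 0.35) / (0.6 × 0.9 + 0.4 × s) = (0.351 + 0.14s) / (0.54 + 0.4s).

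Controls, s = 0.60: 0.435 / 0.78 = 55.8%.

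| s in intervention arm | Subset DFS | Difference from controls |
|---|---|---|
| 0.75 | 0.456 / 0.84 = 54.3% | −1.5 points |
| 0.60 | 0.435 / 0.78 = 55.8% | 0 |
| 0.50 | 0.421 / 0.74 = 56.9% | +1.1 points |
| 0.40 | 0.407 / 0.70 = 58.1% | +2.4 points |
| 0.30 | 0.393 / 0.66 = 59.5% | +3.8 points |

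The sign follows whichever way the advice moves frail patients. The table shows only that a difference can arise without a treatment effect, and that it can go either way. It does not estimate anything in this trial.

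**4. The plan's own figure.** The only sample size stated is for the 6-month composite. For 30% versus 20%, two-sided 5% and 80% power, the uncorrected formula gives 294 per arm. With continuity correction it gives 313 per arm, or 626 in all, close to the stated 640. The total is 640 × 1.1 = 704. None of this involves DFS or PFS.

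**5. Method.** A chi-square test on PFS or OS at 24 months uses only whether an event has occurred by then. It ignores when the event occurred and needs a rule for patients lost earlier. The Sample size section assumes that 10% will be lost or lack primary-endpoint data. A time-to-event analysis uses the timing and handles incomplete follow-up by censoring.

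**The case against.** The strongest reply is that this is a drafting slip. The sentence in the design section only gives examples. Table 1 is the formal endpoint list, the abstract agrees with it, and PFS is listed at 24 months. That stands, and it is why the point is minor. It does not remove the conflict, because the example given is absent from the list.

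A reader might go further in four ways that the documents do not support.

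- **That DFS will be compared in a subset selected by the intervention.** No section restricts its population. Applying the primary-endpoint method to secondary endpoints points towards all randomised patients. Counting never-disease-free patients as having an event at time zero would also avoid a subset. The subset problem is therefore conditional.
- **That the label would produce a false benefit.** The Background names suboptimal treatment of older patients as a possible problem. Advice that moves frail patients towards curative treatment is thus as conceivable as the reverse, and the bias would then run against the intervention.
- **That OS is missing from Table 1.** The table lists each component of the primary endpoint at 6, 12 and 24 months, and death is one of them.
- **That the endpoint can be chosen after the results are seen.** This would require the full protocol and the analysis plan, which are not shown, to leave it open as well.

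It is also fair to say that event definitions and censoring rules are normally left to those documents, so their absence is not criticised here. The analysis method is different: the article does state one for secondary endpoints.

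**Conclusion.** The naming conflict is real and sits in the current Methods text. The two terms describe different outcomes in a population where palliative or supportive care is possible. The consequence is limited to a secondary endpoint; the primary endpoint, sample size and randomisation are untouched.

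The conditioning problem arises only if DFS is kept and confined to patients made disease-free, and only if the advice on treatment goal changes who they are. Its direction is then open and its size unknown. Separately, the method stated for secondary endpoints suits PFS and OS poorly, and the same edit can correct it.

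**What to change.** 1. In Study design and setting, replace disease-free survival with progression-free survival. State that it is counted from randomisation to progression or death in all randomised patients.
2. In Statistical analysis, exempt PFS and OS from the method carried over from the primary endpoint. Analyse both to 24 months as time-to-event outcomes in all randomised patients, for example with a log-rank test and a Cox model.
3. If DFS is really intended as an additional endpoint, list it in Table 1 and say how patients never made disease-free are counted.

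The cost is wording in two sections. Table 1 already schedules PFS and death to 24 months, so no new outcome is needed. The analysis does need dates of progression, death and last contact. If progression is known only from the scheduled assessments, one dating rule should apply to both arms.
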